#### Sample size determination

The power calculations are based on a logistic mixed regression model with the prevalence of moderate intensity PA participation as the outcome variable. An appropriate sample size for this study is determined in a similar manner to previous studies which examined effective recruitment and retention of older adults in a PA programme [30]; PA and nutrition intervention for seniors [31]; as well as PA and nutrition intervention targeting middle-aged adults [32]. For the mixed regression analyses when adjusting for the clustering of RCs, a sample size of *n* = 480 participants (240 participants per group) will allow for an 80% statistical power to detect a medium effect size of 10% improvement in PA prevalence (sufficient leisure time PA estimated to be 28% at baseline) [6] by the intervention group relative to the control group at a significance level of 5%. To account for a 20% attrition rate between the two time points (pre and post intervention), a total of *n* = 600 adult women will be initially recruited at baseline. The sample size takes non-respondents into consideration within the duration of the study but without covariate adjustment.

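### The printed sample-size inputs give about 64% power (two-sided) before any clustering, not the 80% claimed after adjusting for clustering

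*Protocol article*

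**What the plan says.** All the core inputs stand in the protocol article under Sample size determination:

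- The calculation is "based on a logistic mixed regression model with the prevalence of moderate intensity PA participation as the outcome variable".
- It is presented as already allowing for clustering: "For the mixed regression analyses when adjusting for the clustering of RCs".
- The analysable sample is 480, that is "240 participants per group".
- The target is a "medium effect size of 10% improvement in PA prevalence", achieved "by the intervention group relative to the control group", with "sufficient leisure time PA estimated to be 28% at baseline" and a 5% significance level. Whether the test is one- or two-sided is not said.
- The claim is that this sample "will allow for an 80% statistical power to detect a medium effect size of 10% improvement in PA prevalence".
- The 480 is then inflated for 20% attrition to 600 recruited. The section adds that covariates were not adjusted for.

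Three other sections bear on this. Recruitment of RCs fixes 30 centres per arm. Recruitment of participants admits only women who report under 150 minutes of moderate leisure activity a week. Statistical analysis plans mixed regression over the two time points.

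**The concern.** The power, the sample size, the baseline prevalence, the difference and the significance level are all printed, so the claim can be checked directly. It fails before clustering enters, although the text says that clustering has been allowed for. Clustering can only cost power, so the true figure on these inputs must lie below the unclustered one.

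This is the article's only power statement. If it is too high, a null result on activity prevalence would be read as stronger evidence of no effect than the design can supply.

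**Working it through.** **Inputs.** n = 240 per group; p1 = 0.28; p2 = 0.38; alpha = 0.05; 60 RCs; 20% attrition (all from the protocol article). Cluster size among analysable women: 480/60 = 8. ICC: not stated, so 0.01 to 0.05 is assumed below.

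**Attrition step.** 480/(1 − 0.20) = 600. This reproduces.

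**Stated power of 80%, no clustering.** Pooled two-proportion formula:

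- mean proportion = (0.28 + 0.38)/2 = 0.33
- SE0 = √(2 × 0.33 × 0.67/240) = 0.0429
- SE1 = √((0.28 × 0.72 + 0.38 × 0.62)/240) = 0.0427
- two-sided power = Φ((0.10 − 1.96 × SE0)/SE1) = Φ(0.372) = 64.5%
- one-sided power = Φ((0.10 − 1.645 × SE0)/SE1) = Φ(0.689) = about 75%

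The 80% does not reproduce. Other two-sided methods agree: unpooled 64.9%, arcsine 64.6%, log-odds 64.2%, simulated chi-square 64.6%, continuity-corrected 60.7%.

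**Sample size for 80%, no clustering, two-sided.** n = (1.96 × √(2 × 0.33 × 0.67) + 0.842 × √(0.28 × 0.72 + 0.38 × 0.62))²/0.10² = 346 per group, against the stated 240. One-sided it is 273.

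**With clustering (assumed ICC).** Design effect = 1 + (8 − 1) × ICC; effective n = 240/design effect.

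| ICC | Design effect | Effective n per group | Two-sided power | One-sided power |
|---|---|---|---|---|
| 0 | 1.00 | 240 | 64.5% | 75% |
| 0.01 | 1.07 | 224.3 | 61.6% | 72.9% |
| 0.02 | 1.14 | 210.5 | 58.8% | 70.5% |
| 0.05 | 1.35 | 177.8 | 51.8% | 64.1% |

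Outside that range, ICC 0.005 gives 63.0% and ICC 0.10 gives 43.1% (two-sided).

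**Difference detectable with 80% power at 240 per group, two-sided.** About 12.1 points unclustered (12 points gives 79.4%). At ICC 0.01, 12.5 points gives 79.9%. At ICC 0.05, 14 points gives 79.3%.

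**Could repeated measures supply the gap?** Approximating the model as baseline adjustment, the variance is multiplied by (1 − ρ²), where ρ is the pre-post correlation:

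- no clustering, ρ = 0.55: effective n = 240/(1 − 0.3025) = 344, power 79.8%
- ICC 0.01, ρ = 0.60: power 80.5%
- ICC 0.05, ρ = 0.70: power 80.3%

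A change-score analysis, with factor 2(1 − ρ), needs about 0.65 unclustered (79.7%).

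**The case against.** **The check is not the planned model.** The article bases its power on a logistic mixed model, and the analysis uses two time points, whereas the check compares two proportions once. This stands in part: a pre-post correlation of about 0.55 or more would bring power to 80%. But no such correlation is stated, and the section says that covariates were not adjusted for. A reader might go further and infer that the entry criterion rules out any gain, because women who are active enough are excluded and baseline status would hardly vary. The documents do not support so firm a statement. The section does not define sufficient activity, and its own premise of 28% at baseline implies that baseline status varies. The gain is unlikely if the two thresholds match; it is not impossible.

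**The 28% may be the wrong control rate.** This also stands. If the entry criterion removes most sufficiently active women, the control rate could be well below 28%, and a 10-point difference would be easier to detect. For 10% v 20%, power is 86.8% unclustered, 82.2% at ICC 0.02 and 75.4% at ICC 0.05. For 15% v 25% it is 78.4%, 72.9% and 65.5%. This does not rescue the sentence as printed, which uses 28%, but it limits what can be said about the women actually enrolled.

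**The ICC may sit in a fuller document.** Agreed: its absence from a condensed article is not a defect in itself, and the finding does not need it, because 80% already fails at ICC = 0.

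**Other readings of the inputs.** Retaining all 300 per group gives 74.2% two-sided. One-sided and unclustered it gives 83.3%, but that drops both the attrition and the clustering that the text says are included. A fall from 28% to 18%, one-sided and unclustered, also gives 83.3%, but it runs against an improvement.

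**Conclusion.** Wrong as written. On the printed inputs, power is about 64% two-sided or about 75% one-sided with no clustering, and lower with any positive ICC; the 80% would need 346 analysable women per group, not 240. This rests on reading the 10% as percentage points and 28% as the control rate.

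The 62%, 59% and 52% figures are illustrations that depend on assumed ICCs and 8 women per RC. A reader might infer that the trial's real power is 52% to 62%, or that it would miss its target effect in four to five of ten repetitions. The documents do not support that: no ICC is given, and the control rate in the enrolled women is uncertain.

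Two further readings are not counted as errors. The effect is called medium, but the article invokes no effect-size scale. Taking 10% as relative (28% to 30.8%, power about 10%) is a strained reading and only a reason to state which is meant.

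**What to change.** Keep the recruitment target of 600 and correct the power sentence under Sample size determination:

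- Replace the 80% with the power the design delivers. On the printed inputs this is at most about 64% two-sided for a 10-point difference. Equivalently, 80% power is available for about 12 points unclustered and about 12.5 to 14 points if the ICC is 0.01 to 0.05.
- State the sidedness, the ICC and its source, the cluster size of 8, and any pre-post correlation relied on.
- Give an expected control rate at 6 months that is consistent with the entry criterion of under 150 minutes a week, and recompute from these values. The final figure should come from the sponsor's own inputs, not from the ICCs assumed here.
- Say that the difference is absolute.

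The cost is a short recalculation and a change of wording, with no change to recruitment or conduct. On the printed inputs the stated power becomes less favourable.

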Adequate levels of physical activity (PA) and a nutritious diet have been recognised as crucial lifestyle factors for the prevention of NCDs [8]. However, based on the National Health Survey, Singaporean women aged over 50 years reported: (1) high levels of leisure time physical inactivity (72%), (2) low levels of regular exercise (16%) and (3) do not meet the recommended levels of PA for health benefit (39%) [6]. Reasons for low levels of participation include: a lack of time due to work and child commitments (47%); perception of doing adequate PA from undertaking housework (23%); and a lack of interest (16%) [6]. Results from the 2010 Singaporean National Nutrition Survey also revealed that a high proportion of Singaporean women aged 50–69 years have macronutrients intake exceeding the Recommended Dietary Allowance (RDA) for energy (58%), total fat (57%), saturated fat (67%), carbohydrate (54%) and protein (71%); but only 62% of them met the RDA for dietary fibre intake [7]. In addition, a lower percentage of these women met the recommended serving guidelines for vegetables (26%), fruits (34%), wholegrains (43%) and fare only slightly better for rice and alternatives (50%) as well as the meat and alternatives food groups (51%) [7].

Most Singaporeans (> 80%), including older adults, reside with their families in dense, affordable public housing [9]. Recreational centers (RCs) are built within this public housing to provide a venue for residents to come together with the intention of fostering community cohesiveness [10]. These RCs are in close proximity and easily accessed, providing an ideal setting to reach the target group and implement and evaluate a community-based PA and nutrition intervention for older women.

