#### Recruitment of participants

A sample of 600 (interventions *n* = 300; controls *n* = 300) women will then be recruited from these 60 RCs. Participants are required to be: (1) female, aged 50 years and above, (2) undertaking less than 150 min of moderate intensity leisure PA per week (self-reported), (3) not have any medical condition that prohibits involvement in a PA programme, and (4) not currently enrolled in other nutrition and PA research studies.

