#### Group PA, nutrition talks, dietary counselling sessions and telephone contact

Bi-weekly, low-intensity PA, strength and balanced exercises sessions will be conducted. There will be bimonthly nutrition talks, bimonthly dietary counselling and monthly follow-up calls incorporating MI. Programme ambassadors will follow-up with participants’ enquires and provide feedback to support the adoption of healthy practices and monitor the progress of their participants’ goals. Participants will be encouraged to do moderate intensity PA for at least 150 min per week and reminded to monitor their daily progress and goals by recording the frequency and duration of PA in a health calendar provided at the commencement of the programme. Goal setting and feedback will be emphasized at all contact points during the intervention.

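### The 28% baseline prevalence behind the sample size is a general-population rate that does not describe women screened to be below 150 min/week of moderate leisure activity

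*Protocol article*

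**What the plan says.** The Sample size determination section of the protocol article bases power on a "logistic mixed regression model with the prevalence of moderate intensity PA participation as the outcome variable". It takes "sufficient leisure time PA estimated to be 28% at baseline", cited to the national survey, and a "medium effect size of 10% improvement in PA prevalence" in the intervention group relative to control. It states that 480 evaluable women, 240 per group, "will allow for an 80% statistical power" at the 5% level after allowing for clustering by recreational centre (RC). Recruitment is set at 600 to cover 20% attrition.

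Three other places bear on the 28%:

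- **Recruitment of participants**, criterion 2, requires women to be "undertaking less than 150 min of moderate intensity leisure PA per week (self-reported"). The Procedure section says this screening is done by telephone.
- **Background**, citing the same survey, gives 72% leisure-time inactivity and 16% regular exercise among women over 50.
- **The intervention description** says participants will be encouraged to do "moderate intensity PA for at least 150 min per week".

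The article never defines *sufficient* in minutes. The Statistical analysis section plans mixed regression over the two time points with clustering, in general terms for all outcomes.

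**The concern.** The planning rate comes from an unselected population, but the trial selects its participants on the same behaviour. The 150-minute mark is the only moderate-PA threshold in the article. It serves both as the upper limit for entry and as the goal of the programme. If it also defines *sufficient*, the eligibility rule removes the women who make up the 28%.

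Two things are at stake. First, this is the only power justification in the article, and its key input belongs to a different population. Second, a binary baseline status that is nearly constant tells the analysis very little. It cannot improve precision, and a group-by-time term in a logistic model of that status would be poorly identified.

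**Working it through.** **1. Where the 28% comes from.** 100% − 72% = 28%. The match with the Background figure is exact and the citation is the same. The article does not state the derivation, so this is an inference.

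**2. What eligibility does to it.** Let x% of the source population do at least 150 min/week of moderate leisure PA, and suppose all of them count among the 28%. After they are excluded, prevalence in the remainder is (28 − x)/(100 − x). The article does not give x, so these values are illustrative:

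- x = 28 (*sufficient* means at least 150 min/week): 0/72 = 0%
- x = 16: 12/84 = 14.3%
- x = 10: 18/90 = 20%

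Any x above zero gives less than 28%.

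**3. The plan's own figure.** For two proportions with pooled variance, two-sided 5% and 80% power:

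n per arm = [1.96·√(2·p̄·(1−p̄)) + 0.8416·√(p1(1−p1) + p2(1−p2))]² / (p2−p1)²

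With p1 = 0.28, p2 = 0.38 and p̄ = 0.33: [1.96·0.6650 + 0.8416·0.6612]² / 0.01 = 346 per arm before any clustering allowance (273 one-sided). The stated 240 is not reproduced. The attrition step is: 480/(1 − 0.20) = 600.

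Adjustment for baseline could bring the two-sided requirement down to 240 only if the baseline-to-follow-up correlation were √(1 − 240/(346·DE)), where DE is the design effect. That is about 0.55 at ICC 0 and about 0.70 at ICC 0.05 (DE 1.35). A nearly constant binary baseline could not supply such a correlation.

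**4. Power at 240 per group over a range of 6-month control prevalence.** The prevalences are assumed, because the article gives none for eligible women. There are 240/30 = 8 evaluable women per RC. With an assumed ICC of 0.02, DE = 1 + (8−1)·0.02 = 1.14, so the effective n is 240/1.14 = 210.5 per arm.

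Power = Φ{[(p2−p1) − 1.96·√(2·p̄(1−p̄)/n)] / √([p1(1−p1)+p2(1−p2)]/n)}

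Example, 10% v 20%: (0.10 − 1.96·0.03480)/0.03446 = 0.922, and Φ(0.922) = 82%.

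The odds ratio implied by 28% to 38% is (0.38/0.62)/(0.28/0.72) = 1.58. Holding it fixed, p2 = 1.58·o/(1 + 1.58·o), with o = p1/(1−p1).

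| 6-month control | 10-point difference: p2 | Power | Odds ratio 1.58: p2 | Power |
|---|---|---|---|---|
| 5% | 15% | 93% | 7.7% | 20% |
| 10% | 20% | 82% | 14.9% | 33% |
| 15% | 25% | 73% | 21.8% | 43% |
| 20% | 30% | 66% | 28.3% | 51% |
| 28% | 38% | 59% | 38% | 59% |

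Without clustering, the 10-point column reads 96%, 87%, 78%, 72% and 64%.

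**The case against.** The strongest reply is that the article does not define *sufficient*. It also calls the powered outcome moderate-intensity participation, which could mean any participation. A woman doing 60 min/week is eligible and would count as active on that reading. The 150 minutes in the intervention section is advice to participants and not an outcome definition. Screening is by telephone, whereas the outcome comes from the Global Physical Activity Questionnaire (GPAQ) at a later meeting. Table 2 lists incidental as well as programmed activity under that instrument, so some women could be classed as active at baseline.

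All of this stands, and it rules out a flat statement that baseline prevalence is 0% by design. It does not rescue the 28%. With a lower leisure-time threshold, excluding the most active women still pulls the rate below the survey value (step 2). Misclassification might push it back up, but the article does not claim or quantify that.

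A reader might also infer that an almost all-zero baseline leaves the trial with nothing to compare. That does not follow. The effect is stated as intervention relative to control, and 6-month prevalence can differ between arms whatever the starting point. Nor does the article specify a group-by-time logistic model of sufficiency, so the identification problem is a risk to avoid and not an error already fixed in the plan.

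Finally, the mis-stated rate is not necessarily harmful. If a 10-point difference holds at a low control prevalence, 240 per group is adequate: 93% power at 5% and 82% at 10%. This also stands, but only on the absolute scale.

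**Conclusion.** The point holds in this form: the 28% is a population rate that conflicts with the trial's own eligibility rule and should not be used as the baseline prevalence of the enrolled cohort. Baseline prevalence is near zero if *sufficient* means at least 150 min/week, and otherwise should be below 28%.

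The direction of the effect on power cannot be settled from the article. At an assumed ICC of 0.02, over control prevalences of 5% to 20%, power runs from 93% down to 66% for a fixed 10-point difference, and from 20% up to 51% for a fixed odds ratio of 1.58. These figures assume a two-sided 5% test, 8 evaluable women per RC, the RC as the unit of clustering, and no gain from baseline adjustment.

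The 59% in the 28% row should not be attributed to eligibility. It reflects a separate shortfall: 240 per group does not follow from 28% v 38% even before clustering.

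**What to change.** 1. Define *sufficient* in minutes per week, with the intensity and the GPAQ domains that count. The rest depends on this.
2. Replace the 28% with an assumed 6-month control prevalence in women who meet criterion 2, and give its justification.
3. Restate power at 240 per group over a range of that prevalence (for example 5% to 28%), stating the ICC, the sidedness, and whether the effect is an absolute difference or an odds ratio.
4. Analyse 6-month status by arm in a logistic mixed model with RC clustering, adjusted for continuous baseline GPAQ minutes, so that nothing depends on a nearly constant binary baseline.

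The cost is a change of wording and a re-run of the power calculation. The baseline minutes are already collected. The article reports recruitment as ongoing at submission, so the definition could still be fixed before analysis.

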### Outcome measures

Table 2 summarises the outcome variables and how they relate to their corresponding measurement tools.

**Table 2 Tab2:** Primary and secondary outcome variables and measuring tools

**Primary outcome variables**	**Measurement tools**
Self-reported levels of PA behaviour (incidental, programmed and sedentary)	GPAQ
Objectively measured levels of PA: intensity, duration and frequency	ActiGraph GT3X accelerometers
Self-reported levels of dietary behaviours on wholegrains, fat, oils, salt, sugar, fruits and vegetables consumption	STEPS dietary behaviour questionnaire
Lipid profile – cholesterol and TG, BG	Fasting blood samples
**Secondary outcome variables**	**Measurement tools**
Anthropometric measurements – weight, height, BMI, waist hip circumference and body fat percentage	Portable stadiometer, calibrated weighing machines, tape measures and Endo Body Fat Composition Analyser E-DBS908
BP	Omron electronic BP monitor
Self-reported health-related QOL	SF-8 questionnaire

*BG* blood glucose, *BMI* Body Mass Index, *BP* blood pressure, *GPAQ* Global Physical Activity Questionnaire, *PA* physical activity, *QOL* quality of life, *SF* Short Form, *TG* triglyceride

#### Primary outcome variables

##### Self-reported PA behaviour

will be obtained through the administration of the Global Physical Activity Questionnaire (GPAQ), a widely used instrument specifically developed by the World Health Organisation (WHO) for population-wide PA surveillance, and is available in the Chinese language [33]. This instrument has acceptable measurement properties and was used in the National Health Survey to collect data on Singaporeans aged 18–69 years on PA levels [6]. In Singapore, this tool has demonstrated fair-to-moderate correlations for moderate-to-vigorous PA for validity and moderate levels of reliability [34].

##### Accelerometers

(ActiGraph GT3X) [35] will be explained and fitted to the intervention participants. They will wear this device on their right hip for seven consecutive days at baseline and 6 months (post intervention) and remove it when sleeping, showering or doing water-based activities. Data collected will be downloaded using the ActiLife 6 software. This information will be summarised into daily average counts (counts per min) and duration of activity (min per day) at specific intensity levels (inactive, light, moderate, and vigorous) [36].

##### Self-reported dietary eating habits

will be assessed through a WHO-developed, standardized STEPS dietary behaviour questionnaire to monitor the main NCD risk factors [37]. This is a feasible, low-cost nutrition assessment tool comprising 21 questions measuring dietary consumption of wholegrains, fat, oils, salt, sugar, fruits and vegetables for the past week [26].

#### Blood samples

A fasting (> 10 h) blood sample will be collected from the antecubital vein of all participants by trained phlebotomists into appropriate vacuum tubes [38]. All blood analysis will be carried out at the Quest Lab pathology laboratory using an Abbott Architect auto-analyser according to the manufacturer’s instructions. The assays for TC, triglyceride (TG) and glucose are all based on standard enzymatic colourimetric methodology [39, 40]. Serum low-density lipoprotein-cholesterol (LDL-C) will be calculated by the modified Friedewald equation and non-HDL-C will be calculated by subtracting the HDL-C from the TC [41, 42].

#### Secondary outcome variables

##### Weight

will be measured (wearing light clothing without shoes) using a calibrated electronic scale and recorded to the nearest 0.01 kg while *height* will be measured with a portable stadiometer to the nearest 0.1 cm (barefooted) [43, 44].

##### Body Mass Index

(kg/m^2^) will be calculated as weight in kilograms divided by the square of height in metres [45].

